#### Primary research question

Does participation in a structured follow-up consultation with the general practitioner lead to increased utilization (initiation, continuation) of rehabilitation aftercare measures or programs by patients four months after completion of MR?

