### Study design and data collection

#### Rehabilitation patients

In the first phase of the study, we will collect qualitative data in interviews with MR patients to evaluate comprehensibility and user-friendliness of the patient communication aid, which is intended to support study participants during the follow-up consultation with their GP. Participants will be presented with the draft version of the communication aid. In all sections, respondents will be asked to explain to what extent the individual items are comprehensible and whether there are any suggestions for rewording or other modifications. The procedure is based on the cognitive interview methodology and the “think aloud” method [43, 44].

In the second study phase, we will collect quantitative data (written questionnaires) in six inpatient rehabilitation centers in Northern Bavaria and neighboring regions. Questionnaire data will be collected longitudinally at three measurement points (T1: end of MR; T2: after follow-up consultation with GP (intervention group only; four to eight weeks after completion of MR); T3: four months after completion of MR).

The primary outcome is the self-reported utilization (initiation/continuation) of rehabilitation aftercare at T3 (four months post-rehabilitation). Self-reported work ability at T3 is assessed as a secondary outcome. We will collect additional variables to describe the sample and/or include them in moderator or predictive analyses. Table 1 summarizes the instruments used at each measurement point.

**Table 1 Tab1:** Instruments used in the study

Variable	Measure	T1 Completion of MR		T2 After follow-up consultation (IG only)		T3 4 months after completion of MR	
		IG	CG	IG	CG	IG	CG
Rehabilitation aftercare motivation, expectations	single items developed for this study	**X**	**X**				
Rehabilitation aftercare self-efficacy	single items developed for this study	**X**	**X**				
Rehabilitation aftercare recommendations by MR facility	single items developed for this study	**X**	**X**				
Evaluation of medical rehabilitation outcomes (subjective success of rehabilitation)	single items developed for this study	**X**	**X**				
Self-reported work ability	WAS [45, 46]	**X**	**X**				
Health-related quality of life	EQ-5D 5 L [47]	**X**	**X**				
Health literacy	HLS19-Q12-DE [48]	**X**	**X**				
Perceived communicative self-efficacy in patient-physician interactions	Single item developed for this study, based on Maly et al. [49]	**X**	**X**				

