### Sample size

#### Rehabilitation patients

We expect an effect of the intervention on patients’ self-reported use of rehabilitation aftercare four months after they have completed MR (primary outcome). Specifically, we assume that more patients in the IG will use or continue to use aftercare services than patients in the CG. Since CG patients also receive follow-up recommendations from their MR facility, we expect a small effect in favor of the IG.

Utilization of the GPI aftercare programs (IRENA, other) is around 30% [3, 56], which can be used as a minimum approximation for the control condition. We assume an additional utilization rate of 10% as a result of the intervention, i.e. 40% in total. This estimate is exploratory and, given the lack of data, rather conservative.

To calculate the sample size for the cluster randomized crossover trial, we used the Shiny CRT Calculator program [57, 58]. Our estimate for the intra-cluster correlation (ICC) is based on results from a study using GPI routine data for various medical indications (*n* = 653,081) [59]. In this study, researchers developed a risk adjustment strategy to improve the use of return to work as a quality indicator for medical rehabilitation. The ICC for the rehabilitation department level (i.e. indications) averages 1.95% (0.0195).

For six cooperating facilities (clusters), a sample size of 29 participants per cluster (clinic) and time period (intervention/control phase; see Fig. 1) is calculated with a power of 0.8 to demonstrate a small intervention effect, i.e. 174 persons for both the intervention and control conditions (total *n* = 348).

We calculated an expected dropout of approximately 35% from T1 to T2. Due to a lack of data from comparable studies, we used willingness to participate in various medical rehabilitation or aftercare studies as a proxy for willingness to participate in the follow-up consultation [23, 60–68]. Willingness to participate in these studies ranged between 42% and 85% (mean: 67%). Moreover, presumably not all study participants will take part in the follow-up consultation and its use is also contingent upon the participation of the respective GPs. On this basis, we assume a realistic dropout rate of 35%.

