The motivation of participating GPs could be a possible confounder, as GPs who consider medical rehabilitation and follow-up care to be effective and relevant are likely to conduct their consultations differently to those who do not. This issue will be addressed by randomizing patients at the cluster level (i.e., rehabilitation clinics) and by providing a structured consultation guide. In addition, the online survey of GPs will also contain questions about their level of information and attitudes towards medical rehabilitation and aftercare.

The degree to which participating GPs implement the intervention (using the consultation guide) will be assessed using relevant items in the online survey and is also indirectly documented via the patient survey. As mentioned above, the organizational procedures (recruitment, data collection, etc.) are communicated to the participating rehabilitation centers in a standardized way to ensure treatment integrity at the facility level.

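### The 35% T1-to-T2 dropout is expected non-attendance at the consultation, possible only in the intervention group; counted as attrition in both conditions, it makes T2 n = 435 impossible and leaves N = 669 unsupported

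*Protocol article*

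**What the plan says.** All references are to the protocol article.

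- **Sample size, Rehabilitation patients.** The base requirement of 29 per clinic and period, 174 per condition and 348 in total "is calculated with a power of 0.8 to demonstrate a small intervention effect". The 30% utilization rate is one "which can be used as a minimum approximation for the control condition", and the effect is given as: "We assume an additional utilization rate of 10% as a result of the intervention, i.e. 40% in total".
- **Same section, losses.** "We calculated an expected dropout of approximately 35% from T1 to T2". The rate rests on willingness to take part in other rehabilitation or aftercare studies (42% to 85%, mean 67%), used as a proxy for willingness to attend the consultation. Two further reasons follow: "presumably not all study participants will take part in the follow-up consultation", and attendance depends on the patient's GP joining. A further 20% is lost from T2 to T3. The result is N = 669 at T1 and n = 435 at T2.
- **Study design and data collection.** The second measurement is "T2: after follow-up consultation with GP (intervention group only; four to eight weeks after completion of MR". Table 1 marks T2 as not applicable to controls and shows the primary outcome at T3 in both groups.
- **Randomization.** Controls have no study consultation, and every participant of a facility takes the condition of that facility's phase.
- **Primary research question.** "Does participation in a structured follow-up consultation with the general practitioner lead to increased utilization"
- **Discussion.** GP motivation is named as a possible confounder, with the answer: "This issue will be addressed by randomizing patients at the cluster level".

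**The concern.** The 35% describes whether the intervention is taken up. A patient who skips the consultation, or whose GP declines, can still return T3 and so supply the primary outcome. Controls cannot fail to attend a consultation they are never offered. The dropout chain treats both as lost patients.

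Two things follow. First, the stated 669 and 435 do not follow from the design, and the sponsor cannot tell from the text which effect the trial is powered for. Second, a sizing that counts non-attenders as gone, with a primary question worded on participation, fits a comparison of attenders with all controls. Such a comparison would lose the protection of clinic randomisation that the Discussion relies on, because patients and GPs opt in only in the intervention condition.

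**Working it through.** **Inputs from the protocol article:** 174 per condition (348 in total), power 0.80, 30% versus 40%, ICC 0.0195, 35% T1-to-T2 loss, 20% T2-to-T3 loss.

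**Assumptions, not stated there:** two-sided 5% test; equal enrolment per condition; the 20% taken as the T1-to-T3 loss in everyone; a cluster autocorrelation of 1. With the last, the crossover design effect is 1 + (m − 1) × ICC − m × ICC = 1 − 0.0195 = 0.9805 for any cluster-period size m, so power depends on the number analysed alone. A lower autocorrelation would reduce power.

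**1. The plan's own figures.** 348/0.80 = 435; 435/0.65 = 669.2. Both reproduce, so the 35% was applied to the two conditions together.

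**2. Can T2 reach 435?** With 669 enrolled, 669/2 = 334.5 are in the intervention condition and due a T2. If 65% of them attend, 334.5 × 0.65 ≈ 217 T2 forms follow a consultation. Neither number is 435.

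**3. Who would be present at T3?** Attenders in the intervention group: 334.5 × 0.65 × 0.80 ≈ 174. Controls: 334.5 × 0.80 ≈ 268. An attenders-only comparison would hold 174 + 268 = 442 patients. With everyone kept, 669 × 0.80 ≈ 535 are analysed. Neither total is 348.

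**4. Enrolment on the plan's base of 348.**

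| Reading | Calculation | Enrolment |
|---|---|---|
| All by allocation; 10 points is the effect of the offer | 348/0.80 | 435 |
| 35% applied to the intervention group only | 174/(0.65 × 0.80) + 174/0.80 = 334.6 + 217.5 | about 552 |
| All by allocation; 10 points holds in attenders only, none in non-attenders | 348/0.65² ≈ 824 analysed; 824/0.80 | about 1,030 |

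**5. Power at 669 enrolled (about 535 analysed).** Take the plan's claim of 80% at 348 as given. The standardised effect is then 1.960 + 0.842 = 2.802 at 348. It scales with the square root of the number analysed: √(535.2/348) = 1.240.

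- Effect of the offer 10 points: 2.802 × 1.240 − 1.960 = 1.51, power about 93%.
- Effect diluted to 0.65 × 10 = 6.5 points: 2.802 × 0.65 × 1.240 − 1.960 = 0.30, power about 62%.
- The same at the ends of the plan's willingness range: 42% attendance gives 2.802 × 0.42 × 1.240 − 1.960 = −0.50, about 31%; 85% gives 2.802 × 0.85 × 1.240 − 1.960 = 0.99, about 84%.

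**The case against.** The strongest reply is that the text nowhere removes non-attenders, and several places point the other way. Randomization assigns all participants of a facility to its condition. The expected effect is worded as intervention group against control group. Recruitment has the centers mail T2 and T3 to study participants with no attendance condition. The T2 form asks whether the consultation was used, which makes sense only if some respondents did not use it. An article may also leave the definition of the analysis set to a fuller document. This stands: a reader might infer that an attenders-only comparison is planned and that the primary result will be biased, but the documents do not establish it. Nor do they give aftercare rates in attenders and non-attenders, so the size of any such bias cannot be derived.

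A reader might also infer that keeping non-attenders must dilute the 10 points. The text leans against that. The sample size section gives 40% for the condition as a whole, and the GP estimate applies 40% to all rehabilitation measures (0.40 × 34,513 ≈ 13,805). On that reading there is no dilution.

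The total of 669 can also be defended as what equal enrolment needs to yield 174 attenders. That is true arithmetically, but it presupposes the attenders-only comparison, gives about 442 patients at T3 rather than 348, and still does not produce 435 at T2.

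None of these replies rescues the calculation. If non-attenders stay in the comparison, counting them as lost is wrong.

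**Conclusion.** The point holds as an error in the stated sample size. The 35% is non-attendance, arises in one condition only, and is applied to both as attrition. T2 n = 435 cannot occur. N = 669 does not follow from the base of 348 under analysis by allocation: 435 would be enough if the 10 points apply to all invited patients, and about 62% power is available at 669 if they apply to attenders only. The second figure assumes 65% attendance, no gain in non-attenders and the assumptions listed with the calculation.

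Bias in the primary comparison is a possibility left open by the sizing and by the wording of the primary question. It is not a plan stated in the text.

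One matter is separate. The base of 348 does not itself reproduce from 30% versus 40% with six clusters. Power recomputed directly from those rates is lower than shown here, and that further shortfall is not caused by the 35%.

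**What to change.** 1. Take the 35% out of the dropout chain and call it expected non-attendance in the intervention group. Keep only T3 non-response as loss.
2. State that the 10 points are the effect in all invited patients. If they are meant for attenders, restate the power for the diluted effect.
3. Correct 669 and 435 to match. This is a restatement and does not call for more enrolment. The lower figure of 435 should not be used to cut recruitment before the base of 348 has been checked.
4. State that every T1 participant is analysed in the condition of the clinic's phase, whether or not the consultation took place or T2 was returned, and confirm that T3 goes to all of them.
5. Word the primary question as the effect of being offered the consultation.

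An additional analysis of the effect in attenders, using allocation as the instrument, is optional. The cost is a few sentences of protocol wording. Mailing T3 to all participants appears to be intended already. The one substantive consequence is that the effect of the offer may be smaller than the effect among those who attend.

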#### General practitioners

For the group of general practitioners, the following estimates of the number of participants can be made:

The number of GPs in the study region among whom the potential study participants (patients) are distributed (i.e. how many GP practices would need to be included) can only be roughly estimated. There are 3,050 GPs in Northern Bavaria [78]. There is no care or billing data available on how many of the patients receiving primary/GP care are currently employed or at least 18 years old and thus eligible to participate in the study. Therefore, we cannot rely on specific proportions or frequencies here.

The starting point for estimating the sample size is the following data: The GPI North Bavaria provided a total of 34,513 medical rehabilitation measures in 2024 and 10,096 aftercare services in the form of IRENA, T-RENA (Trainingstherapeutische Rehabilitationsnachsorge; Training/Exercise Therapy Rehabilitation Aftercare), and Psy-RENA (Psychosomatische Rehabilitationsnachsorge; Psychosomatic Rehabilitation Aftercare) [56]. This means that about 30% of patients make use of such aftercare services. Assuming that an additional 10% of patients use aftercare as a result of the intervention (i.e. a total of 40%, corresponding to *n* = 13,805), based on the estimated number of cases for rehabilitation patients (see above, *n* = 348), *n* = 77 GPs in northern Bavaria would be required as study participants to carry out the intervention.

The interviews with GPs during the development of the consultation guide will comprise a sample size of 8 to 10 participants. This should reflect a sufficient spectrum in terms of medical practice size and the number of patients.

The following considerations regarding sample size are used for the online survey to answer the secondary research questions (evaluation of the intervention concept; increase in knowledge of GPs regarding MR and rehabilitation aftercare). An online survey of GPs on medical rehabilitation in the federal state of Schleswig-Holstein had a participation rate of 27.7% (*n* = 194), based on the total number of respondents in the mailing list of the Schleswig-Holstein Association of Statutory Health Insurance Physicians (*n* = 700) [25]. Based on this percentage and the estimates presented above, we assume that 21 GPs will participate in the online survey. It is possible that the willingness to complete the questionnaire is higher due to participation in the study, which would result in a larger proportion of participating physicians.

### Recruitment

In each cooperating rehabilitation center, a responsible person (“study coordinator”) will be appointed, who will be briefed by the research team and be provided with all important information, including inclusion and exclusion criteria, as well as materials for recruitment and data collection (study information, declaration of consent, questionnaires) within the facility. This person will be specifically responsible for contacting eligible patients and asking them to participate in the study, distributing (and collecting) all relevant documents after informed consent to participate in the study has been given, and providing and managing materials related to the intervention (information flyers/vouchers for the follow-up consultation) during the data collection period in which the respective facility is assigned to the intervention condition.

The rehabilitation center will hand out T1 questionnaires to study participants. To ensure anonymity, the respective rehabilitation centers will also mail T2 and T3 questionnaires to study participants (the latter can also be completed online). To simplify their return and to reduce the dropout rate, the envelopes for all questionnaires (T1, T2, T3) are prepaid. The rehabilitation facilities will receive a flat fee of €20 per study participant recruited for their recruitment efforts.

For practical reasons, we will recruit GPs via various channels:

First, the Bavarian Association of General Practitioners will inform GPs about the study (incl. eligibility for reimbursement of follow-up consultations) via the association’s newsletter and other resources, several times if necessary.

In addition to the rehabilitation discharge report, which is sent to the respective GP as standard, the cooperating rehabilitation centers will enclose an information sheet and other written materials that identify the respective patient as a study participant.

The sheet contains information about the study and the follow-up consultation. In particular, it includes a link to the project website, where GPs will complete the evaluation questionnaire after each follow-up consultation.

Study patients will also receive an “information package” containing the relevant study documents as well as information and materials for their GP. When making an appointment for the follow-up consultation, patients will be asked to present the materials to their GP and ask them to participate in the study.

For the interviews with rehabilitation patients in the first study phase, the study coordinators at the cooperating rehabilitation centers will approach potentially eligible patients based on the inclusion criteria (see above) and ask them to participate in the interviews. Once consent to participate has been obtained, an appointment will be scheduled at the rehabilitation center. Whether interview participants will be recruited in all rehabilitation centers or only in some of them will be decided depending on the respective resources and possibilities on site.

For the interviews with GPs in the first study phase, we will contact general practitioners in the Würzburg area whose practices are part of the local network of teaching practices of the Department of General Practice at the University of Würzburg and ask for participation.

### Retention strategies

We consider the following procedures as important in order to achieve a high participation rate among patients: The questionnaires for study participants are pre-franked to facilitate return mailing. The study team will design the questionnaires as short as possible so that the effort for participants to complete them is relatively low. The invitation to participate in the study comes from the rehabilitation facility, which patients are likely to view as a trustworthy institution. Recruitment will focus on the benefits of the intervention in terms of an additional, low-threshold offer for patients provided by their GP.

No concomitant care or interventions are prohibited during the conduct of the study.

To ensure treatment integrity at the facility level, the organizational processes (recruitment, data collection, etc.) will be communicated uniformly and thus standardized.

The following procedures are intended to encourage GPs to participate in the study: The intervention will be reimbursed as a medical service. The intervention and study participation are supported and endorsed by the Bavarian Association of General Practitioners and the Bavarian Association of Statutory Health Insurance Physicians. GPs will be provided with tools to help them implement the intervention (consultation guide, easily accessible billing mode).

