A written patient communication aid will be developed to support patients in the follow-up consultation. Where appropriate and useful, it will reflect the content and structure of the GP consultation guide. The communication aid is intended to help patients reflect on the following topics: current state of health; perceived changes and improvements as a result of MR; achievement of rehabilitation goals; implementation of aftercare recommendations. It is designed to encourage patients to ask questions and express their preferences during the follow-up consultation based on the modified PACE framework [39, 40], and to clarify their health-related values [41, 42].

Intervention group participants will receive a written invitation to the follow-up consultation. In order to increase the commitment and attractiveness of the follow-up consultation, the invitation will be communicated as a ”Let’s talk about your health” voucher (including the patient communication aid). The specific distribution of the invitation and accompanying materials depends on when and by whom the follow-up recommendations are provided in the respective rehabilitation facilities, for example, during the final medical consultation. This will be clarified in the first study phase.

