### Randomization

Using a two-period cluster randomized crossover design, study participants (rehabilitation patients) will be randomized at the facility level: during the first nine months of data collection, the intervention will be carried out in half of the cooperating rehabilitation centers (clusters), i.e., all study participants in these facilities are assigned to the intervention condition. In the other half of clusters, the control condition is implemented. After nine months, the clusters cross so that the intervention condition will now be implemented in the previous “control clusters” and vice versa (Fig. 2). Which facilities enter the intervention or control phase first is determined in advance by randomization.

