**Fig. 2 Fig2:**
[figure not shown]
Crossover design. Note: MR = medical rehabilitation

Participants in the intervention group (IG) and the control group (CG) will receive the usual recommendations for rehabilitation aftercare during their rehabilitation stay. Participants in the IG will also receive an invitation for the follow-up consultation with their GP, which is scheduled to take place four to eight weeks after completion of MR. Participants in the control group (CG) do not receive a follow-up consultation with their GP.

Given the small scale and effort of the intervention required on the part of the rehabilitation centers, we do not expect any carry-over effects and see no need to introduce a washout period before the change of conditions in the facilities [55].

The study staff will randomly assign the clusters using an online research tool (Research Randomizer; randomizer.org).

There will be no blinding of healthcare professionals in the rehabilitation centers or GPs, as knowledge of the status of study participants (intervention / control condition) is necessary for the provision of information and materials (rehabilitation centers) or the intervention (GPs). The study team will inform the rehabilitation centers of their respective allocation in written form so that they can organize study materials and procedures accordingly.

On the part of rehabilitation patients, study participants will be blinded with regard to group assignment (intervention/control condition). Due to the nature of the study, we do not expect that emergency unblinding will be necessary.

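### Coordinators who know the clinic's current condition recruit with a benefit-led message that does not fit control phases, so the two conditions can enrol different patients

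*Protocol article*

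**What the plan says.** All references are to the Methods of the protocol article.

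- **Allocation comes first and is uniform within a phase.** Randomization: "Which facilities enter the intervention or control phase first is determined in advance by randomization". For clinics in the intervention phase, "all study participants in these facilities are assigned to the intervention condition".
- **The clinic knows its phase.** Same section: "The study team will inform the rehabilitation centers of their respective allocation in written form", and "There will be no blinding of healthcare professionals in the rehabilitation centers or GPs".
- **The clinic recruits.** Recruitment, on the study coordinator: "This person will be specifically responsible for contacting eligible patients and asking them to participate in the study". The coordinator also manages the flyers and vouchers "during the data collection period in which the respective facility is assigned to the intervention condition".
- **The message.** Retention strategies: "Recruitment will focus on the benefits of the intervention in terms of an additional, low-threshold offer for patients provided by their GP".
- **Control condition.** Randomization states that control participants get no GP follow-up consultation within the study.
- **Counterweights.** Retention strategies says that organisational processes, recruitment among them, are communicated uniformly, for the sake of treatment integrity at facility level. Randomization says that patients are blinded to their group.
- **Timing of the voucher.** Intervention: "The specific distribution of the invitation and accompanying materials depends on when and by whom the follow-up recommendations are provided". The final medical consultation is given as an example, and the matter is left to the first study phase. T1, which records aftercare motivation and self-efficacy, is taken at the end of rehabilitation.

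**The concern.** In a cluster trial with individual recruitment, randomising the clinics protects the comparison only if the people who enrol do not depend on the condition. Here the recruiter knows the condition of every next patient, and the stated focus of recruitment is an offer that exists in only one condition. Each clinic contributes to both conditions, which balances stable clinic characteristics. The patients in the two periods are different people, however, so the crossover does not balance who agrees to take part.

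The primary outcome is self-reported use of aftercare, which plausibly depends on how motivated a patient already is. A difference between conditions in the motivation of those who enrol would therefore appear as a difference in the outcome. T1 motivation and self-efficacy could reveal such a difference, but only if they are measured before the patient sees intervention material.

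**Working it through.** The article gives no figure for selection at enrolment, so there is none to reproduce. The only yardstick is the planned effect in Sample size: 40% − 30% = 10 points.

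**Step 1: what the text implies under each reading of the message.**

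| Reading | Consequence |
|---|---|
| Message differs by phase (offer stressed only in intervention phases) | Patients consent to different propositions, so the enrolled groups can differ. A patient can infer the group from the pitch, so the blinding is doubtful. |
| Same benefit-led message in both phases | Patient self-selection is smaller, but control patients hear of a benefit they will not receive. The recruiter still knows the phase, and differential dropout is a risk. |

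The article does not say which reading applies. Neither is satisfactory.

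**Step 2: an illustration of size. All inputs in this step are assumptions except the 30% control rate, the ICC of 0.0195 and the 174 per condition, which come from Sample size.**

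Assume no true effect. Let half of control enrolees be motivated, and let the motivated share be δ higher in intervention phases. Let aftercare use be a in motivated and b in unmotivated patients. Then

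- control rate = 0.5a + 0.5b
- intervention rate = (0.5 + δ)a + (0.5 − δ)b
- spurious difference = δ(a − b)

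The three pairs (a, b) are chosen so that the control rate is 30% each time, e.g. 0.5 × 0.45 + 0.5 × 0.15 = 0.30. For δ = 0.10 with 45%/15%: 0.6 × 0.45 + 0.4 × 0.15 = 0.33, and 0.33 − 0.30 = 0.03.

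The false-positive rate uses n = 174/(1 − 0.0195) ≈ 177.5 effective patients per condition. This is the most favourable crossover case, with the within-clinic correlation fully shared between periods. It also uses a two-sided 5% test (assumed, as the article states no level) and SE = √[p_C(1 − p_C)/n + p_I(1 − p_I)/n].

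| Use, motivated / unmotivated | δ = 10 points | δ = 20 points | δ = 30 points |
|---|---|---|---|
| 40% / 20% | 2 points (7%) | 4 points (13%) | 6 points (23%) |
| 45% / 15% | 3 points (9%) | 6 points (23%) | 9 points (43%) |
| 50% / 10% | 4 points (13%) | 8 points (36%) | 12 points (66%) |

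Cells show the spurious difference, with the false-positive rate in parentheses. If selection ran the other way (δ negative), the spurious difference would have the opposite sign and could hide a real effect.

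**The case against.** The strongest reply is that the article already points to a common procedure. Recruitment processes are to be communicated uniformly and patients are to be blinded, so the sentence may mean no more than describing the trial and the offer under study in the same way to everyone. The exact script would normally sit in the full protocol and information sheet, which are not shown. This has weight: the article nowhere says that the wording changes with the phase, and a reader should not infer that it does. But uniform processes do not hide the phase from the recruiter, and a uniform message that focuses on the intervention's benefits is still inaccurate in control phases. The objection is to a sentence that is stated, not to a script that is absent.

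Three stronger readings are tempting and are not supported.

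- **That the bias favours the intervention.** An offer of support may attract patients keen on aftercare, but a low-threshold offer could equally draw patients with barriers or low motivation. The document cannot settle this.
- **That T1 is contaminated by the voucher.** The order of T1 and voucher is openly deferred to the first study phase, so it is an open point and not an error. The Recruitment section also places the handing out of study documents after informed consent, and the invitation goes to people already in the intervention group. The moderators named under Statistical methods are age, sex and health literacy. Motivation and self-efficacy are covered only by a general remark on additional variables.
- **That the trial will be off by a particular number of points.** The figures above depend wholly on assumed inputs.

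**Conclusion.** The point holds as a weakness in how recruitment is described. A recruiter who knows the phase, working with a message centred on an offer available in one condition only, allows the conditions to enrol different patients. The counterweights in the text do not remove this. Size and direction cannot be determined from the article. Across the assumed scenarios the spurious difference runs from 2 to 12 points, so it could be small or could match the whole planned 10-point effect. That range shows why the matter deserves attention; it is not an estimate for this trial. The point should be corrected before recruitment because it is cheap to do so and because selection at enrolment cannot reliably be repaired in the analysis.

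**What to change.** 1. Replace the sentence in Retention strategies by a commitment to one neutral script and one information sheet, word for word the same in both phases, for example: 'some patients will be offered an additional GP consultation'.
2. When voucher distribution is settled in the first study phase, require consent and a completed T1 questionnaire before the voucher is shown or handed out. T1 motivation and self-efficacy are then true baseline values and can be compared between conditions.
3. Optionally, have the coordinator tally eligible, approached and consenting patients per clinic and period, and compare the tallies between conditions.

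The cost is rewording recruitment material, one ordering rule and, if adopted, a simple count by staff already in place. The neutral wording may lower the consent rate somewhat. It also leaves the coordinator unblinded, so it reduces the risk of differential selection without removing it. The baseline comparison and the tally are there to show what remains.
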